## Randomization

Employer–employee dyads are randomly assigned to either the intervention or control group in a 1:1 ratio with random block sizes. Neither the participants nor the researchers will be blinded. Randomization is performed in Castor EDC [25] using variable block randomization to reduce the predictability of the random sequence. The executing researcher (DB) will conduct the randomization upon receiving the informed consent forms. In instances where multiple participants require randomization at the same time, another researcher will conduct the randomization. Allocation concealment will be ensured in Castor EDC, with the release of the randomization code only occurring after the completion of all baseline measurements. The allocation to the intervention or control group will be definitive, with no possibility of reversal.

### The intervention

The SME tool comprises of an open-access website targeting the employer of the sick-listed employee. The website provides practical resources, including templates, communication videos and information on legislation, possible workplace accommodations, and tailored tips on how to support employees with most common reasons of sick leave. In line with legislation [22] and based on previous experience with an online employer tool for supporting employees with cancer [26], information is tailored to different phases of sick leave: (1) the time of reporting ill, (2) short-term sick leave (≤ 6 weeks), (3) long-term sick leave (> 6 weeks), (4) RTW, and (5) follow-up care. A comprehensive overview of the intervention’s development, objectives, and elements will be available in a publication elsewhere [13]. In brief, the SME tool has been developed using the IM approach, incorporating insights from stakeholders: (walk-through) interviews with employers (*N* = 14) and focus groups with employees (*N* = 12) and OPs (*N* = 12) [27]. The SME tool aims to improve the intention and ability of SME employers to provide appropriate support during sick leave and RTW, thereby enhancing the satisfaction of long-term sick-listed employees with the received support from their employer. The desired change of employer behavior, aimed at providing RTW support, is outlined in a logical model of change (see Additional file 1) using the Self-Determination Theory [15, 16, 26]. This theory resonates with distinct characteristics inherent to SME employers, and its three key components are connected to the targeted behavior changes. To begin, the relatedness component aligns with the familial structure often found in SMEs, such as fostering good communication [8]. Subsequently, the autonomy component is associated with aligning actions with company norms and values, emphasizing independence and flexibility in decision-making—a crucial aspect in the dynamic SME environment. For instance, engaging the right stakeholders and experiencing freedom in doing so. Finally, the competence component aligns with the essential skills and knowledge for tasks such as providing practical RTW support.

## Intervention group

After the inclusion of the employee–employer dyad, the SME tool is provided to the employers randomized to the intervention group. The executing researcher (DB) will provide these employers with an e-mail containing their unique website’s URL and details of the study. Employers are asked to use the SME tool during the 6 months follow-up. They will receive an e-mail after 1 and 3 months reminding them to use it, although its usage is not mandated. There are no criteria for discontinuing the allocated intervention.

## Control group

The URL of the SME tool will remain undisclosed to employers in the control group, ensuring that employers and employees will receive care as usual from their OP. The study will be conducted in the Netherlands. For details regarding the Dutch context and thus the usual care for the control group, we refer to Table 1. During the course of the study, online search engines will not be able to trace the SME tool to prevent possible contamination from the intervention group to the control group. All participants are permitted to receive concomitant care or interventions.

### Data collection

Self-reported questionnaires will be distributed digitally to employees and employers using the electronic data capture system Castor EDM [35], prior to randomization (baseline; T0), and after 1 (T1), 3 (T2), and 6 months of follow-up (T3). E-mail and phone reminders will be sent after 1 and 2 weeks, respectively. All data is securely saved in Castor EDC [35], processed in SPSS 25.0 [28], and stored on the secure sponsor’s surfer. The executing researcher (DB), principal investigator (FG), and project leaders (MG and ST) will be given access to the final data sets. No prior adverse events have been reported during digital employer interventions [17], and we do not anticipate any. However, should any adverse events occur, we will report them through the sponsor’s portal at the Amsterdam UMC.

## Participant characteristics and effect measures

### Employees

At T0, the questionnaire contains questions about the personal and work-related characteristics of the employee (e.g., age, gender, reason for sick leave, educational level, work status, type of contract, type of work). Measures for effect evaluation will be assessed as change from baseline at each time point (i.e., T0, T1, T2, and T3), except for one time to event: *total number of sick leave days*. Table 3 depicts an overview of all outcome variables.

**Table 3 Tab3:** An overview of primary, secondary, and process outcome variables

Level	Construct	Measurement instrument; # items	Example item	Response categories	Score calculation
Primary outcome variable					
Employee	Satisfaction with the RTW support from employer	Questionnaire; Self-developed; 1 item	How satisfied are you with the sick leave and return to work guidance you have received from your employer since the sick leave/over the past month/3 months?	1) Very dissatisfied, 2) dissatisfied, 3) neutral, 4) satisfied, and 5) very satisfied	N/A
Secondary outcome variable					
Employee	Social support from employer	Questionnaire; Self-developed; 8 items	How important is it that your employer provides emotional support during sick leave and RTW? (importance); how much emotional support have you perceived form your employer? (amount of support)	1) Very unimportant, 2) unimportant, 3) neutral, 4) important, and 5) very important; 1) Very few, 2) few, 3) neutral, 4) much, and 5) very much	“Importance score” multiplied with “amount of support score” leads to “weighted score”, with higher scores indicating more social support from employer
	Total number of sick leave days	Questionnaire; Self-developed; 8 items	Have you worked in the past month/3 months? This can include both activities in your regular job as well as in adapted work	Yes or no options and open-ended responses to express current employment status, for example date input (e.g., return to work since:../../….)	The average number of working days per week divided by the contracted work days
	Work performance	Questionnaire; Maastricht Instrument for Sustainable Employability (MAISE), subscale 2A ‘work performance’; 6 items	I have the knowledge to perform my job well	1) Completely disagree, 2) disagree, 3) neutral, 4) agree, and 5) completely agree	Mean score, with higher scores indicating better work performance
	Quality of Working Life	Questionnaire; Quality of Working Life Questionnaire for cancer survivors (QWLQ-CS), subscale 2 **“**understanding and recognition in the organization”; 5 items	My supervisor understands my health situation and possible complaints	1) Completely disagree, 2) disagree, 3) somewhat disagree, 4) somewhat agree, 5) agree, and 6) completely agree	Mean score, with higher scores indicating higher quality of working life
Employer	Self-efficacy	Questionnaire; Empowerment Questionnaire, subscale “the competence scale”; 3 items	Supporting an employee who has reported ill is a significant responsibility for me	1) Completely disagree, 2) disagree, 3) somewhat disagree, 4) somewhat agree, 5) agree, and 6) completely agree	Mean score, with higher scores indicating more self-efficacy
	Satisfaction with the resumption of work of the respective employee	Questionnaire; Self-developed; 1 item	How satisfied are you with the work resumption process of your employee since the sick leave/over the past month/3 months?	1) Very dissatisfied, 2) dissatisfied, 3) neutral, 4) satisfied, and 5) very satisfied	N/A
Process evaluation					
Employer	Recruitment	Questionnaire and logbook of in- and exclusion of (potential) participants; Self-developed; 1 item	What is your reason for not participating?	Open-ended	N/A
	Use of the SME tool	Questionnaire and tracking software (Piwik PRO); Self-developed 6 items	How often have you visited the SME tool in the past three months?	Open-ended, multiple-choice options, and website usage	N/A
	Perceived usefulness of the SME tool	Questionnaire; Self-developed; 9 items	Would you recommend the tool to other employers when guiding an employee who has reported sick?	Open-ended and multiple-choice options	N/A
	Components of the logic model of change	Questionnaire; Self-developed; 3 items	I have the skills to support an employee on sick leave	1) Completely disagree, 2) disagree, 3) somewhat disagree, 4) somewhat agree, 5) agree, and 6) completely agree	Individual scores represent the overall score of individual components, with higher scores indicating higher autonomy, competence, relatedness and ability
	Experiences	Topic list; Self-developed; 5 items	Potential implementation strategies for the national implementation of the SME tool	Open-ended	N/A
Employee	Recruitment	Questionnaire and logbook of in- and exclusion of (potential) participants; Self-developed; 1 item	What is your reason for not participating?	Open-ended	N/A
	Experiences	Topic-list; Self-developed; 5 items	Potential implementation strategies for the national implementation of the SME tool	Open-ended	N/A

*N/A* not applicable

The primary outcome will be the *employee satisfaction with the RTW support from employer*, measured with a 1-item rating: “How satisfied are you with the sick leave and return to work guidance you have received from your employer since your sick leave/over the past month/3 months?” scored on a 5-point Likert scale, from very dissatisfied to very satisfied. The category represents the score, with higher scores indicating higher satisfaction. Satisfaction, in this context, refers to the general attitude towards experiences encountered [23]. Similar inquiries on job satisfaction or satisfaction with specific job aspects are commonly addressed in scientific literature [29, 30].

Secondary outcomes on the level of the employee include: Social support: social support is assessed through the four facets of support potentially provided by the employer, i.e.: (1) emotional support, (2) practical support, (3) informational support, and (4) appreciative support [23, 31]. The measurement comprises eight questions regarding the importance and amount of support received. The mean score of the importance and amount of support are analyzed separately to take into account the individual difference between the perceived importance. Multiplying all the “importance scores” with each corresponding “amount of support score” leads to a total “weighted score”. A higher score indicates higher social support from the employer, collectively assessing the overall level of social support provided by the employer [32].Total number of sick leave days: the total number of sick leave days involves the assessment of the average number of working days per week over the preceding 4 weeks and the total number of (partial) sick days. This is measured with questions about the current employment status, continuity in the same organization and job position, recent work activities, and details about returning to work if applicable [33]. The total number of sick leave days status is calculated by dividing the average number of working days per week by the contracted work days (T0–T3). Additionally, the total count of (partial) sick days is obtained by measuring the time interval between the initial day of illness and the date of resuming work.Work performance: work performance is measured with subscale 2A from the Maastricht Instrument for Sustainable Employability (MAISE) and refers to the long-term capacity of employees to actively participate in and contribute to the workforce [34]. The six statements, only filled in if work activities have been done in the past 4 weeks, are measured on a 5-point Likert scale. The mean score of the total sum is calculated, with higher scores indicating higher work performance. These scales have demonstrated reliability and validity across diverse employee populations [34].Quality of working life: quality of working life is measured with subscale 2 from the Quality of Working Life Questionnaire for cancer survivors (QWLQ-CS). This validated questionnaire comprises items designed to capture dimensions of work-related perceptions and is measured on a 6-point Likert scale. Only subscale 2 about “understanding and recognition in the organization” consisting of five items is included, as we only anticipate change in this subscale according to our logic model of change (Additional file 1). The sum represents the overall score, with a higher score corresponding to a higher feeling of understanding and recognition in the organization. The questionnaire’s internal consistency, construct validity, and group-level reproducibility have been established, rendering it suitable as a patient-reported outcome measure for interventions [35, 36]. The questionnaire has also been applied beyond cancer-related contexts, such as in cases of chronic inflammatory bowel disease [37].

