### Participants

We aim to include 202 employer–employee dyads, thus a total of 404 participants. Both employees and employers will receive a voucher of 20 euros after participating in the study, i.e., when all questionnaires are completed. Employees at study enrolment should:Be of working age (18–65 years);Have a fixed or temporary employment contract at a SME (≤ 250 employees), with a minimum of 6 months remaining in their contract;Be currently sick-listed or partially sick-listed (≤ 8 weeks), with a risk of long-term absenteeism, based on the likelihood of the duration of sick leave exceeding 2 months as assessed by their occupational physician (OP, in plural OPs);Be able to understand and read Dutch sufficiently, in order to complete the questionnaires;Not have a colleague who is already participating in the study.

Subsequently, the employer of the participating employee will be included. At the time of study entry, the employer should be:An employer, supervisor, (case)manager, or HR manager of a SME (≤ 250 employees). In this study, the employer is appointed by the employee and refers to the person who is in direct contact with the employee, and thus the person who offers the RTW support to the employee;Able to understand and read Dutch sufficiently, in order to use the SME tool and complete the questionnaires.

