
### Statistical analysis

All data will be analyzed according to the intention-to-treat (ITT) principle, as well as the per-protocol (PP) principle [17]. The latter analysis is conducted by tracking the analytics of the website usage through Piwik PRO at least one time if randomized to the intervention group [39]. Due to the nature of the intervention, blinding of participants is not possible. Therefore, the trial is open-labeled. However, data analysis will be performed by a researcher who is blinded to the arms. Primary and secondary outcomes and participants’ characteristics for effect evaluation will be assessed using descriptive statistics. *P*-values ≤ 0.05 will be considered statistically significant. Longitudinal linear mixed models (LMM), including random intercepts and random slopes for each OP, will be used to examine differences between the intervention and control groups for the continuous primary outcome measures as well as all continuous secondary outcome measures: social support from the employer, work performance, quality of working life, self-efficacy, and satisfaction with the resumption of work of the respective employee. Kaplan–Meier survival analysis and Cox regression analysis will be used to compare the time from the first day of sick leave to RTW between the intervention and control groups. In the Kaplan–Meier survival analysis, we will censor patients who dropped out of the study. Covariate adjustment will be performed in the models to account for factors such as gender and age that appear to be prognostic for the outcome measures. We will report reasons for dropout for each randomization group and compare the reasons quantitatively and qualitatively. Dropouts will be included in the analysis by modern imputation methods for missing data. The interviews for the process evaluation will be recorded, transcribed verbatim, and thematically analyzed using MaxQDA [40]. The statistical analyses, including data preparation, will be conducted using SPSS 25.0 and R [28, 41].

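### Work performance is scored only for employees who have recently worked, yet the plan analyses it as change from baseline and compares it between arms by LMM under ITT

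*Protocol article*

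**What the plan says.** All statements are in the protocol article.

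- **Completion rule** (Employees, secondary outcomes), on the work performance subscale: "The six statements, only filled in if work activities have been done in the past 4 weeks".
- **Effect measure** (Employees, opening paragraph): "Measures for effect evaluation will be assessed as change from baseline at each time point (i.e., T0, T1, T2, and T3"). One exception is named, sick leave days. Work performance is not exempted.
- **Model** (Statistical analysis): linear mixed models with random effects per occupational physician compare the arms on the primary outcome and on "all continuous secondary outcome measures: social support from the employer, work performance, quality of working life" and the employer-level measures.
- **Analysis set** (Statistical analysis): "All data will be analyzed according to the intention-to-treat (ITT) principle, as well as the per-protocol (PP) principle".
- **Missing data** (Statistical analysis): "Dropouts will be included in the analysis by modern imputation methods for missing data". Nothing is said about items that do not apply because the employee is not working.
- **Work status at entry** (Participants): "Be currently sick-listed or partially sick-listed (≤ 8 weeks"), with sick leave judged likely to last beyond 2 months.
- **Return to work (RTW)**: time to RTW is compared between arms by Kaplan–Meier and Cox (Statistical analysis). The logic model places sustainable RTW at the end of the path that starts with better employer support (Methodological considerations).

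**The concern.** The completion rule, the effect measure and the analysis set do not fit together for this outcome.

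At baseline, some participants cannot have a score, so the change the plan asks for is undefined for them. This follows from the eligibility criteria combined with the completion rule, not from non-response.

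After randomisation, having a score depends on having worked in the last 4 weeks. That status arises after allocation and may differ between arms. Comparing scores among those who have one is then a comparison of two selected subsets, although the plan labels it intention to treat. Suppose the tool brings back employees who would otherwise still be absent, and they perform less well at first. The intervention mean then falls with no harm done by the tool. The opposite selection would flatter it.

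The result would be tested at P ≤ 0.05 and read as a randomised effect on performance.

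**Working it through.** **1. Who has a score**

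| Employee | T0 score | T1–T3 score |
|---|---|---|
| Partially sick-listed and working | yes | if worked in the 4 weeks before the visit |
| Fully absent, less than 4 weeks at T0 | possible, as they worked within the look-back window | same condition |
| Fully absent, more than 4 and up to 8 weeks at T0 | none | same condition |

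The document gives no share for any row.

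**2. The plan's own figure.** There is none for work performance. The sample size for the primary outcome is used below only as a base. Two means, difference 0.53, SD 1.05, two-sided 0.05 (assumed), power 80%: 2 × (1.05 × (1.960 + 0.842) / 0.53)² = 61.6, so 62 per arm. With 160/40 = 4 employees per physician and ICC 0.1, the design effect is 1 + 3 × 0.1 = 1.3, and 62 × 1.3 = 80.6, against 80 stated. Then 80.6/0.8 = 100.75, so 101 per arm and 202 dyads, as stated. This approximates the plan's slope model, and the point does not depend on it.

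**3. Information, if change literally needs a T0 score.** Of 80 per arm, a T0 score in 20, 40, 60 or 80% (assumed) leaves 16, 32, 48 or 64.

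**4. Selection, with no true effect on performance.** All inputs are assumed.

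*(a) Mixture.* Let p₀ and p₁ be the shares working in control and intervention, and d the deficit of the extra returners in SD. The shift in the intervention mean among those working is −((p₁ − p₀)/p₁) × d.

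- 60% v 70%, d = 0.5: (0.10/0.70) × 0.5 = 0.07 SD.
- 50% v 70%, d = 0.8: (0.20/0.70) × 0.8 = 0.23 SD.

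*(b) Latent readiness to work.* An employee works if readiness exceeds a cut-off, and readiness correlates ρ with performance. The mean performance among those working is ρ × φ(z)/p, where z is the normal cut-off for share p. The ratio φ(z)/p is 0.966, 0.798, 0.644, 0.497 and 0.350 at p = 0.4, 0.5, 0.6, 0.7 and 0.8. The bias is ρ times the intervention ratio minus the control ratio.

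| Control v intervention | ρ = 0.3 | ρ = 0.5 |
|---|---|---|
| 40% v 40% | 0 | 0 |
| 40% v 50% | −0.05 SD | −0.08 SD |
| 40% v 60% | −0.10 SD | −0.16 SD |
| 60% v 70% | −0.04 SD | −0.07 SD |
| 60% v 80% | −0.09 SD | −0.15 SD |

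Example: 0.5 × (0.644 − 0.966) = −0.16. A simulation of the same model agrees to within 0.002 SD.

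**5. Does the mixed model resolve it?** With T0 as a response, it keeps employees who lack a baseline score. But it treats their absent scores as ignorably missing, and so estimates a mean that includes the performance of people who are not working. For them the score is undefined, not merely unobserved.

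**The case against.** Four stronger readings are tempting, and the document supports none of them.

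- **That baseline is missing for everyone, or for most.** Partially sick-listed employees who work, and those absent for less than 4 weeks, can have a T0 score. Table 3 counts adapted work as work in its sick-leave item. If that definition carries over, the gap narrows further.
- **That half or more of the sample is lost.** That needs a subtraction score or a required baseline covariate. The article lists T0 among the time points and specifies longitudinal models, and its baseline adjustment is stated for satisfaction only. A model with T0 as a response loses nobody for lack of a baseline score.
- **That the plan imputes scores for employees who are not working.** The imputation rule concerns dropouts. An employee who returns questionnaires while off work is not a dropout. The article is silent on this group, and a separate analysis plan might settle it.
- **That the arm comparison is necessarily biased.** It is biased only if the tool changes who is working, or if selection into work differs between arms. The article itself says that sustainable RTW depends on many factors beyond the tool. The upper figure of 0.23 SD needs a 20-point gap in working shares and returners 0.8 SD worse.

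What remains is the conflict between rules the article itself fixes: conditional completion, change from baseline with a single exemption, and an intention-to-treat comparison. A later analysis plan can interpret these rules but cannot make a score exist for someone not at work. This is one secondary outcome among several.

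**Conclusion.** The point holds in this limited form. For employees fully off work for more than 4 weeks at T0, change from baseline in work performance is undefined. At T1 to T3 the arms are compared in sets defined by a post-randomisation status that the trial itself compares between arms through time to RTW.

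Under assumed working shares 10 to 20 points apart, and extra returners who perform worse, the bias is roughly 0.04 to 0.23 SD against the tool. If the extra returners perform better, the sign reverses. If working shares and selection are equal in both arms, the bias is zero, and the cost is lost information and a result that applies only to those at work. Neither direction nor size can be fixed from the document.

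The change should be made, but it touches neither the primary outcome, the sample size nor the randomisation.

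**What to change.** Change the wording in Employees (effect measures and the work performance entry) and in Statistical analysis:

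1. Exempt work performance from change from baseline, alongside sick leave days.
2. State that it is summarised by arm only among employees working at each visit, descriptively, and labelled as a conditional, non-randomised comparison rather than an intention-to-treat effect.
3. Report the number and proportion working, and with a score, by arm and visit.
4. State that imputation of this outcome does not extend to employees who are not at work. This is a clarification, as the current rule addresses dropouts only.

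No new data are needed, because work status is already collected at each questionnaire. The cost is that work performance no longer supports a confirmatory claim about the tool.

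A composite that ranks not working lowest would restore a comparison of all randomised employees. It would also overlap with the time-to-RTW analysis and change what the subscale measures, so it is optional at most.
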